## Abstract

Youth obesity is a strong predictor of adult obesity, which has well-known negative health consequences. Thus, addressing adult obesity requires tackling youth obesity. MED4Youth’s main objective is to strengthen the link between the Mediterranean Diet (MD) and the health benefits against youth obesity and associated cardiovascular disease (CVD) risk factors, identifying positive effects exerted by an MD including sourdough bread and healthy products from the Mediterranean basis (chickpeas/hummus, nuts, and pomegranate juice). For this purpose, a multicenter randomized controlled trial in which an MD-based intervention will be compared to a traditional low-fat diet intervention will be carried out with 240 overweight and obese adolescents (13–17 years) from Spain, Portugal, and Italy. Both interventions will be combined with an educational web-application addressed to engage the adolescents through a learning-through-playing approach, using both educational materials and games. To assess the interventions, adherence to the MD, dietary records, physical activity, food frequency, sociodemographic, and quality of life questionnaires as well as classical anthropometric and biochemical parameters will be evaluated. Furthermore, an omics approach will be performed to elucidate whether the interventions can shape the gut microbiota and gut-derived metabolites to gain knowledge on the mechanisms through which the MD can exert its beneficial effects.

## 1. Introduction

According to the World Health Organization (WHO), youth obesity is one of the world’s most challenging public health problems [1,2]. In 2016, 9.9% of children and adolescents between 5 to 19 y were obese, and about one in five children and adolescents (18.7%) was considered overweight in the Organization for Economic Cooperation and Development (OECD) countries [3]. The prevalence of overweight and obesity in children and adolescents is even higher in some Mediterranean countries, the average rates of overweight and obesity being 32.4% in Portugal, 34.1% in Spain, and 36.8% in Italy [3]. This problem needs compelling solutions, considering that adolescent obesity is a strong predictor of adult obesity, which has many well-known short- and long-term health and economic consequences, both for the individual and for the society as a whole.

The Mediterranean Diet (MD) is one of the healthiest diets worldwide. It is characterized by a balanced lipid profile (low in saturated fats (SFAs) and high in monounsaturated fats (MUFAs), with olive oil as the main source of fat), a high intake of low glycaemic index carbohydrates, fiber, antioxidants, cereals (preferably as whole grain), legumes, fruit, vegetables, and nuts, and a moderate consumption of fish and shellfish, white meat, eggs, and dairy products [4,5,6]. Recently, the environmental impact of MD has been addressed and considered in an updated version of the MD Pyramid, which emphasizes a lower consumption of red meat and bovine dairy products, and a higher consumption of legumes and locally grown eco-friendly plant foods [7,8]. Results from the PREDIMED study clearly demonstrated that an MD supplemented with extra-virgin olive oil or nuts was associated with a reduced risk of cardiovascular disease (CVD) and death compared with a low-fat control diet in middle-aged and elderly participants [9,10]. The beneficial effects of the MD on different components of the Metabolic syndrome (MetS), such as abdominal obesity and circulating levels of glucose [11,12], have also been demonstrated. In addition, different studies have shown that MD can also reduce body weight and adiposity, especially when this diet is energy-restricted [13,14]. According to the results of a recent umbrella review of meta-analyses of randomized controlled trials, the Mediterranean diet had the strongest evidence of a beneficial effect on both anthropometric parameters and cardiometabolic risk factors in adult populations [15]. 

Concerning adolescents, some cross-sectional studies showed that a high adherence to the MD was associated with decreased risk of being overweight, obese, and affected by MetS in adolescents from Mediterranean countries [16,17]. However, the health effects of MD, and the underlying mechanisms, have been scarcely evaluated in obese adolescents through well-designed clinical–nutritional intervention studies. Thus, to the best of our knowledge, there was only a pilot RCT, implemented in 49 Mexican obese children (11 years old), which showed that a nutritional intervention based on MD for 16 weeks was more effective in reducing body mass index (BMI) and in improving lipid profile than a standard diet [18]. Therefore, more nutritional intervention studies carried out in large cohorts of adolescents from different Mediterranean countries are needed to shed more light on the beneficial effects of MD against obesity and CVD risk factors in comparison with conventional low-fat diets.

Adherence to MD is easier with respect to the majority of the prescribed hypocaloric diets, which is mainly due to its variety of foods and flavours [5]. Nevertheless, during the last decades, there has been a constant reduction of this adherence among young people in different Mediterranean countries, now ranging from 10% to about 21% [19,20,21]. In addition, European children spend more and more time watching television, playing video games, or on the internet, which implies a decrease in physical activity and energy expenditure, which is a well-known risk factor for obesity and CVD [22,23]. Therefore, it is essential to combine an MD nutritional intervention with the promotion of physical exercise and with educational strategies addressed to increase the will of the adolescents to be compliant with the dietary advice.

A growing body of scientific evidence suggests that the intestinal microbiota plays an important role in maintaining an optimal health status in the host [24,25]. Alterations in the composition of the gut microbiota that lead to a reduction in beneficial bacteria, also known as dysbiosis, may contribute to the pathogenesis of obesity, insulin resistance, type 2 diabetes, and non-alcoholic fatty liver disease (NAFLD) [5,24,25,26]. The gut microbiota also determines how different key nutrients and bioactive molecules, such as bile acids, lipopolysaccharide (LPS), and short-chain fatty acids (SCFAs), exert their signaling actions [27,28]. Some data suggest that MD, or some of its bioactive ingredients, can positively modulate gut microbiota by influencing its composition [29,30,31,32,33], increasing the abundance of beneficial bacteria such as *Lactobacillus*, *Prevotella*, *Bifidobacteria*, and *Enterococcus,* and decreasing the amount of *Clostridium* and *Bacteroides* [30]. In a pilot study, the adherence to a Mediterranean-inspired anti-inflammatory diet slightly normalized the gut microbiota in individuals with Crohn’s disease [31]. Another study showed that high adherence to MD was associated with increased fecal SCFA concentration, as well as decreased levels of urinary trimethylamine N-oxide, which is highly associated with intestinal dysbiosis and cardiovascular risk [34]. However, as far as we know, how a MD-based nutritional intervention can shape the gut microbiota and modulate the production of gut-derived metabolites, as well as the mechanisms by which MD exert its effects on the intestinal bacterial communities and on human health, is far from being understood, and it has not been yet evaluated in adolescent populations.

All the above commented aspects prompted us to build a multidisciplinary consortium of six partners from five Mediterranean countries, with complementary expertise and resources within the areas of nutrition, biochemistry, ICT/Bioinformatics, omics sciences, and food manufacturing, which was created to implement a strategy to tackle youth obesity (MED4Youth project; https://med4youth.eu/ (accessed on 12 April 2021)). This consortium is constituted by four research institutions: Fundació Eurecat (Reus, Spain), University of Coimbra (UC, Coimbra, Portugal), Università di Parma (UNIPR, Parma, Italy) and Scientific Food Center (Amman, Jordan), and two small and medium enterprises (SMEs), NOVAPAN S.L. (Spain) and Shikma Field Crops (Israel). The MED4Youth project arises with the main purpose of assessing whether an energy-restricted MD intervention including healthy and palatable products from the Mediterranean basin (mixed nuts [10], pomegranate [35,36,37], and hummus [38]) and a multigrain sourdough bread with proven health effects [39] is more effective against youth obesity and associated CVD risk factors than a conventional low-fat diet. To achieve this goal, a multicentric nutritional and clinical intervention study, specifically targeting obese/overweight adolescents (13–17 years) from Spain, Italy, and Portugal will be carried out. The study will include an educational approach based on a web-application designed to encourage healthy behaviors. Furthermore, the project will also include an omics and a system biology approach to elucidate whether the MD can shape the gut microbiota and gut-derived metabolites, to shed more light on the mechanisms by which MD may exert its beneficial effects against youth obesity and CVD risk factors.

## 2. Materials and Methods

### 2.1. Study Design and Setting

The overall design of the study is represented in Figure 1. The MED4Youth study is a multicenter single-blinded randomized controlled clinical trial with obese and overweight adolescents (13–17 y) from Italy, Portugal, and Spain, in which an MD-based intervention will be compared to a traditional low-fat diet intervention. The three centers involved in the study obtained the approval of the Ethics Committee of each institution: (1) Eurecat (study coordinator): Institut d’Investigació Sanitària Pere i Virgili (Ref. CEIM: 210/2020); (2) UNIPR: Area Vasta Emilia Nord (AVEN) Ethical Committee (pre-approval Ref. Prot. 28638); (3) UC: Ethics Committee of Centro Hospitalar e Universitário de Coimbra and Portuguese National Data Protection Commission (Ref. CHUC-197-20). MED4Youth study was registered at ClinicalTrials.gov (NCT04719052). The protocol conformed to the Helsinki Declaration and Good Clinical Practice guides of the International Conference of Harmonization. This study followed the CONSORT criteria.

According to the sample size calculations, a total of 240 volunteers from Italy, Portugal, and Spain will be recruited for this study (80 participants per country).

The Spanish subjects will be recruited by Eurecat in the province of Tarragona, the Portuguese subjects will be recruited by the Hospital Pediátrico de Coimbra, and the Italian subjects will be recruited by the Pediatric Clinic of the Maternal and Child Department of the Parma University Hospital. The 80 individuals recruited in each country will be randomly assigned to either a MD group (n = 120, n = 40 per country), which will be instructed to follow an MD that will incorporate sourdough bread, hummus, pomegranate, and mixed nuts, or a Control group (n = 120, n = 40 per country), which will be assigned to a standard low-fat diet. The intervention duration is 4 months for each participant, including 3 visits. A follow-up visit after 4 months from the end of the intervention will be carried out.

The randomization code will be computer-generated using software (Geoffrey C. Urbaniak and Scott Plous, Lancaster, PA, USA). Furthermore, the unit responsible for the randomization will be separate from the study researchers.

For ethical reasons, a control group with no treatment against obesity will not be included, since a meta-analysis of randomized controlled trials for the treatment of overweight in children clearly demonstrates that control groups, whether wait listed or only given written information, consistently gained weight (2.1% increase in percentage overweight post treatment and 2.7% post follow-up) [40]. Due to the nature of the study, the participants cannot be blinded to the intervention, although the investigators who will perform the sample and data analysis will be.

### 2.2. Selection Criteria

Subjects included in the study:Boys and girls aged 13–17 years,Having obesity, defined as an age- and sex-specific BMI in the 95th percentile or greater (1), or great overweight (age- and sex-specific BMI in the ≥90th to <95th percentile),If they and their parents (or holders of parental responsibility over the child) provide written informed consent (signed by parents and by the adolescent), andHaving easily access to internet (e.g., via mobile phone, tablet, pc).

Exclusion criteria are:Having diabetes and other metabolic, endocrine, and chronic disorders,Intake of antibiotics, drug, probiotics, or nutritional supplements in the last month,Prescribed medicine to control hypertension, inflammation, or dyslipidaemia,Following a prescribed diet for any reason, including weight loss, in the last 3 months,Following a religion-restricted diet, andHaving allergies or food intolerances to nuts, pomegranate, bread, and/or chickpeas.

All volunteers will be examined by physician to assess whether they meet the conditions for inclusion. For this purpose, a medical interview, a physical examination, and laboratory tests will be performed.

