(1)The MD will be based on a high consumption of unsaturated fat from vegetable sources (extra virgin olive oil and nuts) and minimally processed plant foods (vegetables, fruits, nuts, whole grains and legumes), low consumption of meat (especially red and processed meats) and sweets, and moderate consumption of fish and dairy products (mainly yogurt and cheese) [6,43]. Accordingly, this diet will provide a high amount of mono and polyunsaturated fatty acids, fiber, and phenolic compounds [44]. The MD will be based on the one proposed as MD in the PREDIMED study [45], providing 40–45% of energy from carbohydrate, 35–40% from fat, and 15–20% from protein. Special attention will be paid to the benefits of whole and minimally processed foods, traditional food vs. fast food, and seasonal products. Within the MD pattern, the intervention group (MD) will consume a sourdough bread and 3 specific foods from the Mediterranean basin with proven healthy effects (pomegranate juice, chickpeas/hummus, and mixed nuts) (Table 1).

In summary, adolescents in the MD group will replace the intake of conventional bread by sourdough bread consumption (2 servings of 50–60 g daily), they will incorporate into their diet chickpeas (2 servings of 150 g/week chickpeas, a minimum of one of them being hummus), while they will consume at least another serving of legumes, which can be chickpeas or another legume, and will consume pomegranate juice (4 servings of 200 mL/week) and mixed nuts (4 servings of 30 g/week). The sourdough bread will be a multigrain leavened with Rebola sourdough, which has been previously shown to elicit a lower increase in postprandial blood glucose levels and to decrease the inflammatory marker MCP-1 in rats when compared to a conventional white bread [35]. The squeezed pomegranate will be a single-strength juice. It will be squeezed with the arils, seeds, and inner and outer shell in order to get the important polyphenols existing in the fruit. Chickpeas are a popular pulse rich in protein and dietary fiber and will be consumed boiled and as hummus (paste of chickpeas, tahini, olive oil, lemon, and herbs).

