### 2.4. Implementation of the Motivational Interview Technique

Before beginning the intervention, a personalized dietary advice (30-min session) to each participant including recommendations on the desired frequency of intake of specific foods and general recommendations about performing physical activity will be delivered by dietitians/nutritionists by using the psychological “motivational Interview” technique [48]. The motivational interview will have a standardized internal protocol that will follow the dietitians/nutritionists of the 3 each enrolment centers.

In the first session, the attendance of parents, mentors, or caregivers will be recommended, as they can strongly encourage their children and help the adolescents understand and follow the lifestyle recommendations. Especially, parents can help with cooking and with food purchase.

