### 2.6. Manufacturing and Distribution of the Mediterranean Basin Foods

The sourdough bread will be manufactured by NOVAPAN. Afterwards, NOVAPAN will distribute the sourdough bread to the three enrollment centers. These breads will be sent several times to each institution during the study, will be stored at the centers at −20 °C, and will be provided periodically by the researchers of each center to the adolescents (and/or parents of the adolescents) allocated in the MD group. The breads will be provided to the volunteers at no cost, and an extra amount of breads will be given for the rest of family in order to increase compliance.

Chickpeas/hummus and pomegranate juice will be sent by Shikma Field Crops to each center and will be provided to the MD group. Chickpeas/hummus and pomegranate will be sent several times during the study. Hummus and pomegranate will be delivered in refrigerated conditions, while chickpeas will be delivered cooked and canned.

Walnuts, almonds, and hazelnuts will be distributed by the company COSELVA (La Selva del Camp, Tarragona, Spain) to the different centers. The nuts will be packaged by COSELVA in an individual package containing 10 g for each nut (walnuts, almonds, and hazelnuts).

Moreover, extra virgin olive oil (EVOO) will be provided to the MD group in order to ensure that this group uses this type of fat for cooking and dressing. EVOO will be distributed by COSELVA to the different centers.

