## Figures and Tables

**Figure 1 ijerph-18-04841-f001:**
[figure not shown]
(**a**) Design of the Study. (**b**) Overview of the intervention groups. MD, Mediterranean Diet; MED, Mediterranean; BMI, Body Mass Index; ES, Spain; PT, Portugal; IT, Italy; V, Visit; WC, Waist Circumference.

**Table 1 ijerph-18-04841-t001:** Details on the frequency portions of the Mediterranean basin foods.

Specific Food	Frequency of Portions
Pomegranate	It is recommended at least 2 servings/day of fruit: 14–21 servings/week In addition to the fresh whole fruit, 4 servings of pomegranate juice (200 mL) will be consumed during the week.
Hummus and chickpeas	It is recommended 3 servings/week of pulses (150–200 g (50–80 g dry)). Two servings/week must be cooked chickpeas, minimum one of them as hummus, and another serving may be chickpeas or different pulses. The portion size of hummus is 200 g.
Nuts (almonds, walnuts, and hazelnuts)	It is recommended 3 servings/week: 30 g of mixed nuts/serving. Four servings will be consumed to properly combine the 4 food items included in the MD along the week. Mixed nuts will be walnuts, almonds, and hazelnuts.
Sourdough bread	It is recommended 4–6 servings/day of cereals. Two of these must be a serving of sourdough bread (1 serving of bread is approximately 50–60 g [46,47]).

**Table 2 ijerph-18-04841-t002:** Variables to be analyzed.

Variables	Tool	Timeline
Blood pressure, weight, height, BMI, body composition, WC, WHR	Dietitians/Nutritionists	V1, V2, V3, V4
Physical activity	PAQ-A *	V1, V2, V3, V4
Dietary intake	3-day dietary record *	V1, V2, V3, V4
Food habits	FFQ Helena questionnaire *	V1, V2, V3, V4
MD adherence	KidMed questionnaire *	V1, V2, V3, V4
Quality of life	Kidscreen-27 questionnaire *	V1, V2, V3, V4
Sociodemographic data	HBSC questionnaire *	V1
Knowledge on food and nutrition	NK Helena questionnaire *	V1, V3, V4
Microbiota (feces)	16sRNA sequencing	V1 and V3
Gut-derived metabolites (LPS, SCFAs, lactate, bile acids) (feces and/or plasma)	NMR/GC-MS	V1 and V3
Biomarkers of oxidative stress (8-OHdG, F2-isoprostanes) (urine)	ELISA	V1 and V3
Biomarkers of inflammation (IL-6, CRP, TNFα, MCP1, IL-8) (plasma)	Magnetic bead-based multiplex assays Homeostatic Model Assessment for insulin resistance	V1 and V3 V1 and V3
Biomarkers of adipose tissue function (adiponectin, leptin, resistin) (plasma)		
Biomarkers of insulin resistance (plasma)		
Biomarkers of cardiovascular risk (TMAO) (plasma and urine)	UHPLC‑MS	

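### The allergy exclusion does not name sesame, although the study supplies hummus made with tahini and requires it weekly in the Mediterranean diet arm (minor safety wording)

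*Protocol article*

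**What the plan says.** The allergy criterion in Section 2.2 covers "allergies or food intolerances to nuts, pomegranate, bread, and/or chickpeas". Sesame and tahini do not appear in it, and the article does not mention sesame elsewhere.

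Section 2.3 says that chickpeas will be "consumed boiled and as hummus (paste of chickpeas, tahini, olive oil, lemon, and herbs". Table 1 sets the amount: "Two servings/week must be cooked chickpeas, minimum one of them as hummus", with a 200 g hummus portion. Section 2.6 makes the study the source of the food: "Chickpeas/hummus and pomegranate juice will be sent by Shikma Field Crops to each center and will be provided to the MD group".

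Two other exclusions in Section 2.2 could reach the same adolescent: "Following a prescribed diet for any reason, including weight loss, in the last 3 months" and "Having diabetes and other metabolic, endocrine, and chronic disorders". The same section adds a physician assessment for every volunteer, in which "a medical interview, a physical examination, and laboratory tests will be performed". Section 2.4 adds, before the intervention begins, "a personalized dietary advice (30-min session) to each participant including recommendations on the desired frequency of intake of specific foods", with parents encouraged to attend the first session.

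**The concern.** The evident purpose of the criterion is to keep out adolescents who cannot safely eat what the trial gives them. It names the featured foods but not sesame, an ingredient of one of them. Read literally, it does not exclude an adolescent with a known sesame allergy or intolerance who has no prescribed diet in the last 3 months and is not judged to have a chronic disorder. If allocated to the MD arm, that adolescent would be given tahini-containing hummus every week.

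This is a participant-safety question in minors, about a food the trial both prescribes and supplies. There is also a small design consequence. If a sesame problem is recognised only after randomisation, it matters only to MD participants, because the low-fat arm receives no study foods. Any resulting withdrawal or departure from the assigned diet would fall on one arm.

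**Working it through.** **1. The criterion against the supplied foods.**

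| Item in the exclusion | Matching study food | Is sesame covered? |
|---|---|---|
| nuts | mixed walnuts, almonds, hazelnuts | no |
| pomegranate | pomegranate juice | no |
| bread | sourdough bread | no sesame ingredient is stated |
| chickpeas | chickpeas and hummus | only if the word is read to include every hummus ingredient |

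That tahini is sesame paste is the meaning of the word and needs no source. The last row decides the matter. Section 2.3 and Table 1 do use chickpeas as the general term, with hummus as one form of it, so the wider reading is possible. The criterion does not state it, and a person who reacts to sesame but not to chickpeas does not, in ordinary language, have a chickpea allergy.

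**2. The other exclusions.** The prescribed-diet exclusion applies only if an avoidance diet was prescribed within 3 months; avoiding sesame on one's own does not meet it. The chronic-disorder exclusion might take in a serious allergy but does not name food allergy, and an intolerance fits it less well. Each is binding where it applies, and together they narrow the gap without closing it.

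**3. The safeguards and their timing.** The physician assesses volunteers against the stated conditions, which omit sesame. Table 3 puts the eligibility check at visit 0, before randomisation, and visit 1 after it. The dietitian session advises on specific foods, so it presumably follows allocation, but Section 2.4 places it before the intervention starts. A known allergy raised there would come to light before any study hummus is eaten, though probably after allocation.

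**4. Prescribed exposure.** Table 1 gives at least 1 hummus serving a week, and Section 2.5 gives 16 intervention weeks: 1 × 16 = 16 servings per MD participant. For 120 MD participants (Section 2.1) this is 120 × 16 = 1,920 servings if everyone is retained; the sample-size section plans for 20% dropout.

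**5. How many could be affected.** The documents give no prevalence. Assume p = 0.001 to 0.005, purely for illustration.
- Expected MD participants with the condition, before any safeguard: 120 × p = 0.12 to 0.60.
- Chance of at least one: 1 − (1 − p)^120 = 0.113 to 0.452.
- If a share f (0 to 1) is not reached by the two exclusions in step 2: 120 × p × f = 0 to 0.60. The documents do not allow f to be derived.

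These figures count eligible participants, not reactions. Reactions would be fewer, because participants know which foods they are given and can decline them.

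**6. Cost of the rewording.** Expected extra screen failures before 240 are randomised: 240p/(1 − p) = 0.24 to 1.21. The chance of three or more (negative binomial) is 0.002 to 0.122. Both are upper figures at the assumed prevalence, since some of these adolescents would already be excluded.

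**The case against.** The best counter-argument is that the criterion lists foods, not allergens. Its four items match the four featured foods one to one. Bread is itself a composite, so intolerance to bread can only mean intolerance to something in it; on the same reading, chickpeas would cover hummus and its ingredients. The article is a condensed text, and an ingredient-level checklist may stand in the full protocol or the site manual. The diet also includes fish, yogurt and cheese, which the criterion omits too, so it may never have been meant as a full allergen screen. Finally, a physician interview, a dietitian session, personalised menus with food equivalents, unblinded foods and parental consent all stand between the participant and the hummus.

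Much of this stands. The food-based reading is plausible, the session does precede exposure, and the safeguards make an actual reaction unlikely. What does not follow is that the criterion is adequate as written. This is not a detail the article left out: it states the rule and states it incompletely. Fish, yogurt and cheese are not among the foods the study is said to supply, whereas hummus is. None of the safeguards is tied to exclusion for sesame.

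A reader might infer that the article contradicts itself, or that it uses chickpeas in a sense that leaves hummus out. Neither is supported: the wording is incomplete, and Section 2.3 and Table 1 treat hummus as a form of chickpeas. A reader might also take 11% to 45% as the chance of harm in this trial. It is the chance that at least one of 120 MD participants has the condition, under an assumed prevalence and before any safeguard.

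**Conclusion.** The point holds as a minor wording fault in a safety criterion. The rule as stated does not clearly exclude an adolescent who tolerates chickpeas and reacts to sesame, while the MD arm requires a supplied food that contains sesame. The size of the risk cannot be derived from the documents. Under the assumed 0.1% to 0.5% prevalence, between 0 and 0.60 MD participants would be affected, and the true figure may be near zero because those with the most serious known allergy are the likeliest to be caught by the other criteria. The conclusion rests on the literal wording of Section 2.2 and on no fuller criterion being applied in documents not shown. Power and the primary BMI z-score analysis are not affected.

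**What to change.** Reword the criterion to: allergy or intolerance to any ingredient of the supplied study foods, including sesame/tahini. Check it at visit 0, before randomisation, for all volunteers, so that it applies equally to both arms and does not depend on the later dietitian session. The change is one line in the eligibility criteria and one in the visit 0 checklist, plus about one extra screen failure at the upper end of the assumed prevalence. It will not detect allergies that the family does not know of.
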